## Abstract

**Background:**

Obstructive sleep apnoea (OSA) is a sleep-related breathing disorder characterised by the repeated episodic collapse of the upper airway during sleep, resulting in sleep deprivation, giving rise to apnoeas and hypopnoeas. Based on the severity of OSA, there are two primary treatment modalities, continuous positive airway pressure (CPAP) and mandibular advancement appliances (MAA); both are adherence-dependent. MAA is offered to those with mild to moderate OSA and is prescribed as an alternative to patients intolerable to CPAP. However, adherence to MAA treatment is variable and declines over time. Hence, the current study aims to assess the effectiveness of the stage-matched intervention, the Health Action Process Approach (HAPA), on adherence to MAA in patients with OSA.

**Methods:**

A single-centre randomised clinical trial will be undertaken at Bart’s Health NHS Trust. Fifty-six participants with newly diagnosed OSA are planned to be enrolled in the study and randomised to intervention care (IC) and standardised care (SC) groups. Participants in the SC group will receive routine care whilst participants in the IC group will receive the stage-matched intervention, developed using the HAPA model. Data indicating MAA adherence will be collected both objectively and subjectively, from micro-sensors embedded in the MAA design and sleep diaries, respectively at 3, 6, 18 and 36 months. In addition, a range of questionnaires designed to assess risk perception, outcome expectancy, and self-efficacy (SEMSA) and quality of sleep (PSQI and ESS) and life (EQ-5DL), socio-economic and social support scales will be used.

**Discussion:**

The currently available treatments for obstructive sleep apnoea depend entirely on the patient’s acceptance and use. There are several factors that affect cooperation and wear for example patients’ awareness of their condition, social support and psychological behaviour. In addition, mood, such as anxiety, stress, and depression, may affect wear. At the same time, we know that interventions involving more education and behaviour approaches can help patients adapt more easily to some treatments. As a result, the present trial aims to explore the potential role of these factors to maximise treatment success and minimise side effects.

**Trial registration:**

ClinicalTrials.gov NCT04092660. Registered on September 6, 2019

**Supplementary Information:**

The online version contains supplementary material available at 10.1186/s13063-021-05582-1.

## Administrative information

The order of the items has been modified to group similar items (see http://www.equator-network.org/reporting-guidelines/spirit-2013-statement-defining-standard-protocol-items-for-clinical-trials/).

Although initial subjective treatment adherence to MAA therapy is relatively high, it is declining over time. A phone-based survey of 69 patients with mild to moderate OSA prescribed MAA, reported a 32% adherence rate after 4 years of therapy, indicating a high level of non-adherence [12]. The study also suggested the prevention of barriers, associated with MAA therapy adherence, to improve the efficiency of the appliance and disease outcome. In a systematic review, Hoffstein et al. (2007) reported a wide range of (4–76%) adherence rates in the first year of appliance use and further studies have highlighted that adherence decreases with time [13]: 83% after 1 year [14] and 62–64% after 4–6 year [15, 16].

MAA adherence might differ depending on the type of the appliance, custom-made or ready-made, disease severity, and perhaps patient management [17]. In a recent systematic review, patient-reported adherence (6.4–7 nights per week and 5–6.3 h per night) and preference (*p* ≤ 0.001) were strongly associated to custom-made MAA in comparison to ready-made MAA [18]. Subjective side effects such as dry mouth, excessive salivation, tooth discomfort, muscle tenderness, and jaw stiffness, have never lead to treatment discontinuation [19–22]. In addition, tooth movement and occlusal changes have been seen in objective measurements after 1 to 4 years of follow-up, but these changes have not been reported as being related to treatment withdrawal [23–27].

Dieltjens et al. (2013) were the first to investigate the impact of type D personality disorder on adherence to MAA therapy. Individuals with Type-D personality often possess a negative outlook towards life and are overwhelmed with emotions such as stress, anxiety, and anger. The study assessed 113 patients using two questionnaires: type D scale 14 and a postal questionnaire addressing side effects and adherence to MAA. The study included 83 patients with a baseline type D personality and reported a 45% non-adherence rate amongst them [14]. Patients with a type D personality had a higher discontinuation rate and lower adherence. These findings are in agreement with similar observations reported by Brostrom et al. (2007) in regards to lower CPAP adherence with type D personality [28]. Nevertheless, the study has some limitations. The first limitation of the study is the relatively small sample size (sample bias) and the non-meaningful comparison groups, which may reduce the generalisability of the findings. The second limitation is the subjective assessment of adherence and perceived side-effects rather than employing objective means of adherence measurements. A further limitation is that the characteristic negative reporting trait of the type D patients may cause them to overestimate their non-adherence [14].

Research shows that adoption of a new health behaviour, like a new physical activity routine or adhering to a prescribed medication regimen, is a challenging endeavour involving a variety of social, emotional, and cognitive factors [29]. A multicentre study examined perceived effectiveness, self-efficacy and social support among 122 adult patients with OSA aged ≥ 65 years prescribed for MAA therapy [30]. With a 30% response rate (*n* = 39), the study reported low rates of perceived effectiveness, self-efficacy and social support highlighting the lack of self-efficacy, expectations for positive outcomes and social support experienced by the older patients in the sample. These findings are debatable as literature has identified psychological and social factors and cognitive perceptions as determinants of CPAP adherence, including patients’ risk perceptions, treatment outcome expectations, locus of control, and self-efficacy [31–33]. Another possible limitation of the study is that the questionnaires were mailed to the participants, who were only contacted once by the authors explaining the poor response rate. As a result, further research involving larger samples of men and women incorporating modes, which increase the response rate, is necessary to gain a better understanding of the patient's perception of MAA therapy. In turn, this understanding could be implemented for the development of interventions enhancing patient's adherence and experience to MAA treatment.

Interestingly, previous studies in the field of Sleep Medicine have featured an aspect of enhanced patient education ranging from telephone support to home visits, motivational enhancement, or augmented support [34, 35], which have been proven to effectively improve CPAP adherence when compared to usual care. Bakker et al. (2016) conducted a randomised controlled trial of CPAP use, with motivational enhancement (ME) or CPAP only in 83 participants, with moderate to severe OSA. The trial demonstrated a clinically significant increase in CPAP adherence in the intervention arm (CPAP with ME), supporting the use of a motivational enhancement approach to optimise the management of OSA [36].

A recent Cochrane review has also emphasised the efficiency of interventions in enhancing adherence to CPAP by stating that educational, supportive and behavioural interventions increase CPAP usage to varying degrees [37]. Stage theories such as the Health Action Process Approach (HAPA), a social cognition model for behaviour change, can be used to identify factors to target in an intervention and their interrelationships. The model-based approach often uses a quantitative, questionnaire-based approach to assess a small set of factors linked within a model specifying how the factors are related to behaviour and to one another. It includes self-efficacy, outcome expectancies, and risk-perception as distal predictors, intention as a middle-level mediator, and volitional factors (such as action planning) as the most proximal predictors of behaviour. All are considered as determinants of adherence in CPAP therapy [38, 39].

A number of randomised controlled trials within medicine have examined the concept of stage-matched interventions based on HAPA, for example in the context of dietary behaviours [40], physical activity [41] and dental hygiene [42]. In order to investigate the efficiency of interventions on CPAP adherence, 110 OSA (AHI ≥ 15 events/h) patients were randomly assigned into staged-match intervention care (SMC) and standardised care (SC) groups [4]. The staged-match intervention care design, following the principles of HAPA, significantly improved CPAP adherence whilst facilitating intention formation and enhancing treatment self-efficacy. Although the evidence for stage theories is somewhat inconsistent, a meta-analysis [43] suggests that tailoring interventions to behavioural stages is more effective than a generic, non-staged-tailored approach.

The above stage theory advocates that behaviour intervention takes account of the stages of change. Individuals are presumed to progress through an ordered set of stages whilst contemplating, initiating, and maintaining health behaviour change [44]. Risk perception is an antecedent, that forms an intention to adopt a precautionary action or treatment [4]. After a treatment intention develops, it transforms into detailed action plans and these plans may promote moving further into action and/or a maintenance stage [45] implies that understanding behaviour change over time, on dynamic variables instead of static variables, would achieve maximum intervention effectiveness [4]. This feature differentiates stage theories from social cognition theories, such as the theory of planned behaviour (TPB), which interpret behaviour change as a continuous process.

The approach also recommends a distinction between pre-intentional motivational processes and post-intentional volitional processes [42]. The motivational phase comprises of growing risk perception and outcome expectancies, leading to the development of an intention. Although risk perception is the initial step for developing an intention, it alone is deficient and outcome expectancies, characterised by the advantages and disadvantages of the health behaviour in context are essential to promote intention formation. For example, the more a patient feels vulnerable to the possible health threats of long-term untreated OSA (hypertension, cardiovascular diseases), the more he or she will expect from the MAA therapy.

In the volitional phase, Intention and behaviour implementation (adherence to MAA) would be mediated through action planning [46]. Action planning consists of specifying when, where and how to perform the behaviour [47]. Self-efficacy is an important construct to consider for behaviour change [48] and facilitates maintenance of action [46]. For example, after a patient is provided MAA treatment, he or she would make concrete plans concerning the commencement and continuation of the treatment whilst overcoming the difficulties. Highly self-efficacious individuals are more confident in coping with setbacks and easily tackle unanticipated difficulties, as opposed to individuals with low self-efficacy (Bandura, 1997). Since patients with OSA experience different mindsets from initiation to long-term adherence, it is imperative to frame interventions to optimise adherence, tailor-made to the patients’ specific psychological variables at different stages of therapy [4].

In summary, research on increasing adherence to mandibular advancement appliances in obstructive sleep apnoea patients in underrepresented, which is in sharp contrast to the literature regarding CPAP adherence. Thus, we aim to address this shortfall by identifying the factors influencing adherence to MAA in patients with OSA and simultaneously assess the effectiveness of stage theories/stage-matched intervention on subjective and objective adherence, using the HAPA model.

### Objectives {7}

#### Primary objective

##### Aims and research questions

The aim and primary outcome of this study is as follows:
To assess the effectiveness of stage-matched intervention on adherence to mandibular advancement appliances (MAA) in patients with obstructive sleep apnoea (OSA).

##### Secondary objectives

The secondary outcomes are as follows:
To identify the psychosocial and socio-economic indicators enhancing adherence of MAA in patients with OSA.Use of the indicators to develop a psychological and socio-economic predictor model.

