#### Primary endpoint

Adherence i.e. the number of the hours the patient uses the appliance every night will be measured both objectively and subjectively at 3, 6, 18 and 36 months to assess the effectiveness of the interventions in enhancing adherence to MAA.

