### Sample size {14}

A minimum sample size of 56 patients distributed in two groups is proposed for given α (0.01) and power (0.9), for 2 randomly assigned groups, intervention care (*n* = 28), standard care group (*n* = 28). Finally, assuming a maximum of 15% dropout, a total number of 64 patients is required.

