## Statistical methods

### Statistical methods for primary and secondary outcomes {20a}

Both objective and subjective data of adherence i.e. duration of the usage of the appliance will be collected at 3, 6, 18 and 36 months will be analysed to assess the effectiveness of Intervention care in comparison with standardised care.

Comparison of pre- and post-treatment scores of ESS, SEMSA, PSQI, and EQ-5D, for both the groups, will aid in identifying significant differences in terms of improvement.

Statistically, evaluate the ability of the variables -self-efficacy, risk perception, outcome expectancy, social support and socio-economic position, to predict patient adherence at 3, 6, 18 and 36 months.

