#### Assessing the aims of the study

In order to assess the aims of the study, we will test each of the repeated measures first by themselves using a repeated measures ANOVA controlling for groups:
Adherence – reported, times 3, 6, 18, 36 difference 3–6, 6–18, 18–36Adherence – objective, times 3, 6, 18, 36 difference 3–6, 6–18, 18–36ESS, time 6, difference 0–6PSQI, time 6, difference 0–6EQ5D, time 6, difference 0–6Risk perception, times 3, 6, difference 0–3, 0–6, 3–6Outcome expectancy, times 3, 6, difference 0–3, 0–6, 3–6Self-efficacy, times 3, 6, difference 0–3, difference 0–6, 3–6

Once we understand the trends in the data, we can construct multiple regressions for Adherence variables. These can be the final measures from time 6 or the differences between them and previous times, 0 or 3. In these models, we will use the Psychosocial variables and socio-economic as predictors, beyond the group classification.

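### The predictor model is to be built by multiple regression with at least six terms, after the data trends are seen, on about 54 to 64 patients, so its predictive performance will be overstated unless it is corrected for optimism

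*Protocol article*

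**What the plan says.** All references are to the protocol article.

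- **Product.** Secondary objectives has two parts: finding the indicators that enhance adherence, and then "Use of the indicators to develop a psychological and socio-economic predictor model".
- **Predictors.** Statistical methods {20a} sets out to evaluate "self-efficacy, risk perception, outcome expectancy, social support and socio-economic position, to predict patient adherence at 3, 6, 18 and 36 months". That is five constructs.
- **Method.** Assessing the aims of the study says "we can construct multiple regressions for Adherence variables", and that in these models "we will use the Psychosocial variables and socio-economic as predictors, beyond the group classification". Group is therefore a sixth term.
- **Timing and outcome.** The same section opens this step with "Once we understand the trends in the data" and leaves the outcome open: "These can be the final measures from time 6 or the differences between them and previous times, 0 or 3". Under Primary endpoint, adherence "will be measured both objectively and subjectively at 3, 6, 18 and 36 months".
- **Sample.** Sample size {14}: "A minimum sample size of 56 patients distributed in two groups is proposed", for a comparison of two groups at alpha 0.01 and power 0.9. It then asks for 64 to allow for 15% dropout. The abstract speaks of enrolling 56.

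**The concern.** A predictor model is judged by how well it works in patients who were not used to build it. Ordinary regression with six or more terms on a few dozen patients fits some of the noise in those patients. Its in-sample R-squared is then too high, and its predictions for new patients are spread too widely. The sample size was set for comparing two groups, not for this purpose. Building the model after the trends are seen, with the outcome still open, can only add to the optimism.

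At stake is the second secondary objective. Readers could take the model to explain considerably more of the variation in appliance use than it would in the next patients. The randomised comparison of adherence is not affected.

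**Working it through.** **1. The plan's own figures.** The 56 cannot be reproduced, because no effect size or SD is given. It implies a standardised difference of √(2/28) × (2.576 + 1.282) = 1.03 (two-sided, normal approximation). The 64 follows from 56 × 1.15 = 64.4; dividing instead gives 56/0.85 = 65.9.

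**2. Patients available to the model.**
- 64 recruited: 64 × 0.85 = 54.4, so 54 to 64.
- 56 recruited (abstract): 56 × 0.85 = 47.6, so 48 to 56.

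**3. Terms.** Five constructs + group = 6. Patients per term: 48/6 = 8.0, 54/6 = 9.0, 64/6 = 10.7. There are more terms if the ordinal socio-economic item enters as categories.

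**4. Formulas** (n patients, p terms, true R-squared R, roughly normal predictors):
- apparent R² ≈ 1 − (1 − R)(n − p − 1)/(n − 1)
- R² in new patients = 1 − (1 − R)(n + 1)(n − 2)/[n(n − p − 2)]
- calibration slope ≈ 1 − [p/(n − p − 1)] × (1 − apparent)/apparent

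Example with n = 54, p = 6, R = 0.20:
- apparent: 1 − 0.80 × 47/53 = 0.291
- new patients: 1 − 0.80 × (55 × 52)/(54 × 46) = 1 − 0.80 × 1.151 = 0.079
- slope: 1 − (6/47) × 0.709/0.291 = 0.69

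**5. Results, six terms.** The documents give no value for R, so a range is shown.

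| True R² (assumed) | n | Apparent | New patients | Slope |
|---|---|---|---|---|
| 0 | 48 | 0.128 | −0.174 | – |
| 0 | 54 | 0.113 | −0.151 | – |
| 0 | 64 | 0.095 | −0.124 | – |
| 0.20 | 48 | 0.302 | 0.061 | 0.66 |
| 0.20 | 54 | 0.291 | 0.079 | 0.69 |
| 0.20 | 64 | 0.276 | 0.100 | 0.72 |
| 0.40 | 48 | 0.477 | 0.296 | 0.84 |
| 0.40 | 54 | 0.468 | 0.309 | 0.85 |
| 0.40 | 64 | 0.457 | 0.325 | 0.87 |

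Simulation with independent normal predictors agrees. At R = 0.20 the apparent value is 0.30, 0.29 and 0.27 for n = 48, 54 and 64, and the new-patient value is 0.06, 0.08 and 0.10. At R = 0.40 the apparent value is 0.45 to 0.47, about 0.01 below the approximation. With eight terms (an assumed coding), n = 48 and R = 0.20, the pair is 0.33 and 0.01.

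**6. Behaviour of one fixed model when nothing predicts.** With six terms, adjusted R-squared averages 0.00 and the overall F test rejects in about 5% of simulated trials. Apparent R-squared exceeds 0.20 in 14% (n = 48), 9% (n = 54) or 4% (n = 64).

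**7. Does the proposed correction work?** At R = 0.20, bootstrap optimism correction gives an R-squared of 0.09 to 0.11, against 0.06 to 0.10 in new patients. It is slightly generous but far closer than the apparent 0.27 to 0.30.

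**The case against.** **Silence on shrinkage and validation.** Only a journal article is shown. Such details of a secondary model are commonly left to an analysis plan, and nothing in the article rules them out. That stands: the silence is not an error. The point rests on what the article does state, namely a predictor model as the product, multiple regression as the method, construction after the trends are seen, and this sample.

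**Stronger readings that the documents do not support.**
- A reader might infer that the model will look predictive even when nothing predicts adherence. For one pre-fixed model this is wrong, as step 6 of the working shows.
- A reader might infer that the in-sample fit will be reported as the result, or that the model will be offered as a clinical tool. The article names no performance measure and no such use.
- A reader might take 48 as the working sample. Under Sample size {14} the 64 already allows for dropout, so 54 to 64 is the fairer range. The 48 depends on the abstract's figure.
- A reader might infer chance findings across all the adherence outcomes. Two measures at four times give eight. With all eight modelled and no true association, at least one predictor reaches p < 0.05 in about 68% of simulated trials (n = 48 or 56). That rests on assumed correlations, and the article does not say that all eight will be searched. It supports fixing the outcome early but does not measure the optimism described here.

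**The size depends on an assumed R.** This is also fair. At 0.40 the gap is about 0.13 to 0.16 for 54 to 64 patients, and the model keeps most of its value.

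**Penalised estimation would hinder the first aim.** The predictors are a short list drawn from theory, no stepwise selection is stated, and identifying indicators is an inferential task. Ridge regression would bias those coefficients and complicate their tests. This stands, so ordinary regression should stay for that aim.

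**Conclusion.** The point holds as a cheap improvement to a secondary objective. With six terms and 54 to 64 patients, an assumed true R-squared of 0.20 appears on average as about 0.27 to 0.29 but is about 0.08 to 0.10 in new patients (0.06 if only 48 remain). A calibration slope near 0.7 means predictions spread about 1/0.7 = 1.4 times too widely. The direction is the same for every sample size consistent with the article. The amount rests on the assumed true R-squared, on six terms and on roughly normal predictors; it shrinks with a stronger true signal and grows with more terms. These figures are for one model fixed in advance and do not include any extra optimism from choosing the model or outcome after seeing the trends.

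**What to change.** 1. Before any trends are examined, list one predictor model: the five named constructs plus group, with socio-economic position as a single ordinal score. Name its adherence measure and time point. Models at other times or for the other measure can be reported as supportive.
2. Keep ordinary regression, with its confidence intervals, for identifying indicators.
3. For the predictor model, report bootstrap optimism-corrected R-squared and calibration slope next to the apparent fit. Apply uniform shrinkage to the coefficients if the model is to be used for prediction.
4. Label the model as development only, not validated in other patients.

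The cost is about a day of programming and no new data. The downside is that the reported predictive performance will be lower, and at this sample size the corrected figures will still be imprecise.

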##### Null hypothesis

Stage-matched intervention does not enhance adherence to MAA in patients with OSA compared to standardised care.

